## Abstract

**Background:**

Major depressive disorder (MDD) with atypical features, namely depression with atypical features (AFD), is one of the most common clinical specifiers of MDD, closely associated with bipolar disorder (BD). However, there is still a lack of clinical guidelines for the diagnosis, treatment, and prognosis of AFD. Our study mainly focuses on three issues about how to identify AFD, what is the appropriate individualized treatment for AFD, and what are the predictive biomarkers of conversion to BD.

**Methods:**

The Study of Individualized Diagnosis and Treatment for Depression with Atypical Features (iDoT-AFD) is a multicenter, prospective, open-label study consisting of a 12-week randomized controlled trial (RCT) and a continued follow-up until 4 years or reaching the study endpoint. It is enrolling 480 patients with AFD (120 per treatment arm), 100 patients with BD, and 100 healthy controls (HC). Multivariate dimension information is collected including clinical features, cognitive function, kynurenine pathway metabolomics, and multimodal magnetic resonance imaging (MRI) data. Firstly, multivariate informatics analyses are performed to recognize patients with AFD from participants including the first-episode and recurrent atypical depression, patients with BD, and patients with HC. Secondly, patients with atypical depression are randomly allocated to one of the four treatment groups including “single application of selective serotonin reuptake inhibitor (SSRI) or serotonin-noradrenaline reuptake inhibitor (SNRI)”, “SSRI/SNRI combined with mood stabilizer,” “SSRI/SNRI combined with quetiapine (≥ 150 mg/day),” or “treatment as usual (TAU)” and then followed up 12 weeks to find out the optimized treatment strategies. Thirdly, patients with atypical depression are followed up until 4 years or switching to BD, to explore the risk factors of conversion from atypical depression to BD and eventually build the risk warning model of conversion to BD.

**Discussion:**

The first enrolment was in August 2019. The iDoT-AFD study explores the clinical and biological markers for the diagnosis, treatment, and prognosis of AFD and further provides evidence for clinical guidelines of AFD.

**Trial registration:**

ClinicalTrials.gov NCT04209166. Registered on December 19, 2019.

**Supplementary Information:**

The online version contains supplementary material available at 10.1186/s13063-023-07317-w.

## Administrative information

Note: The numbers in curly brackets in this protocol refer to the SPIRIT checklist item numbers. The order of the items has been modified to group similar items (see http://www.equator-network.org/reporting-guidelines/spirit-2013-statement-defining-standard-protocol-items-for-clinical-trials/).

## Introduction

### Background and rationale {6a}

Currently, there are about 340 million people with major depressive disorder (MDD) worldwide, and the lifetime prevalence rate of MDD is 3.9% in China [1]. The World Health Organization has reported that MDD would become the most serious global burden of disease and eventually turn into a public health problem in 2030 [2].

Depression is clinically heterogeneous, and based on the criteria of the Diagnostic and Statistical Manual of Mental Disorders, Fifth Edition (DSM-5), depressive disorders could be specified with eight kinds of clinical features. Atypical features were incorporated into the DSM-5 as an illness specifier, including mood reactivity, weight gain or appetite increase, hypersomnia, leaden paralysis, and interpersonal rejection sensitivity. MDD with atypical features, namely depression with atypical features (AFD), is one of the most common clinical specifiers of MDD accounting for 15~36% [3]. Rather than a classification of diseases, AFD is a distinctive group of MDD, regarded as a potential indicator for predicting bipolar disorder (BD) or even a variant of BD-II [4–6]. Through our BIPAS survey and review of the literature [7, 8], we found that there is still a lack of evidence from high-quality studies to enhance the clinical guidelines for the diagnosis, treatment, and prognosis of AFD.

From our previous studies, patients with MDD have dysfunctional neural circuits of the frontal cortex, amygdala, hippocampus, and cingulate gyrus, which are closely associated with clinical characteristics [9, 10]. Furthermore, it has been revealed that patients with AFD have increased brain perfusion in the frontal, temporal, and parietal cortex and decreased occipital perfusion [3]. Mediated by inflammatory factors, the tryptophan-kynurenine pathway (KP) can be catalyzed to trigger a series of cascade reactions, and the metabolite products will affect the content and function of neurotransmitters in the brain and participate in the development of depression [11, 12]. In our previous study, the metabolites of KP reduced significantly in patients with MDD and could be used as biomarkers for diagnosis with an accuracy of 83.6% [13]. Recent studies have shown that atypical symptoms are associated with higher levels of kynurenine and tryptophan [14]. Patients with AFD have been found to perform significantly differently than those with melancholic depression on cognitive tasks involving executive function, attention span and persistence, verbal and visual memory, and processing speed [15, 16]. Nevertheless, the findings of studies on AFD are still limited and controversial, possibly due to inconsistent inclusion criteria, small sample, and lack of follow-up. Up to now, no comprehensive clinical guidelines for AFD have been published. Accordingly, there is a need to probe into biomarkers for the diagnosis, treatment, and prognosis of AFD to provide evidence-based guidelines for patients with AFD.

The Study of Individualized Diagnosis and Treatment for Depression with Atypical Features (iDoT-AFD) is a multicenter, prospective, open-label study consisting of a 12-week randomized controlled trial (RCT) and a continued follow-up until 4 years or AFD switching to BD, which is designed based on our previous findings and recent advances in MDD. This paper describes the study protocol of the iDoT-AFD study. The protocol is based on the SPIRIT guidelines for clinical trials (Additional file 1) [17].

### Objectives {7}

The primary aim of the iDoT-AFD study is to identify the molecular imaging biomarkers for AFD by analysis of KP metabonomics and multimodal magnetic resonance imaging (MRI). The secondary aim of the iDoT-AFD study is to find out the optimized intervention and the predictive biomarkers of treatment effectiveness in patients with AFD. The third aim of the iDoT-AFD study is to screen out the risk factors and build a clinical early warning model to predict the conversion of AFD to BD.

### Trial design {8}

The iDoT-AFD study is a multicenter, exploratory, prospective, open-label study consisting of a 12-week parallel-group RCT with an allocation ratio of 1:1:1:1 to evaluate the clinical efficacy of four interventions and a prognosis study focusing on conversion to BD with a maximum of 4 years follow-up (Fig. 1).

**Fig. 1 Fig1:**
[figure not shown]
CONSORT diagram of the study AFD, depression with atypical features; BD, bipolar disorder; HC, healthy control; MRI, magnetic resonance imaging; SSRI, selective serotonin reuptake inhibitor; SNRI, serotonin-noradrenaline reuptake inhibitor; TAU, treatment as usual; RCT, randomized controlled trial

## Methods: participants, interventions, and outcomes

### Study setting {9}

This clinical trial is sponsored by Shanghai Mental Health Centre (SMHC), [name]. Five clinical sites are involved to recruit participants (SMHC, Wuhan Mental Health Center, the Affiliated Brain Hospital of Guangzhou Medical University, Dalian Seventh People’s Hospital, and Xijing Hospital of the Fourth Military Medical University), each with a principal investigator (PI) and a clinical trial coordinator (CTC). The iDoT-AFD study also includes biomedical engineering experts from Shanghai Jiao Tong University and ShanghaiTech University to ensure high-level data mining.

### Eligibility criteria {10}

The inclusion criteria for patients with AFD are as follows: (1) 16–60 years old, (2) meeting the DSM-5 criteria for MDD, (3) scored 20 or higher on the Hamilton’s Depression Scale with 24 items (HAMD-24), (4) enough audiovisual ability and comprehensive ability to accomplish the interview, (5) necessary and appropriate to accept the treatment of antidepressants, (6) scored less than 14 on the Hypomania Symptom Checklist-32 (HCL-32), and (7) meeting DSM-5 specifier for atypical features: mood reactivity and 2 or more of the following—significant weight gain or increase in appetite, hypersomnia, leaden paralysis, and a long-standing pattern of interpersonal rejection sensitivity that results in significant social or occupational impairment.

The exclusion criteria for patients with AFD are as follows: (1) severe medical or neurological problems; (2) previous episodes of mania or hypomania; (3) female patients who are pregnant, planning to be pregnant, or breastfeeding; (4) high risk of suicide; (5) had ECT, MECT, or rTMS in the past 6 months; and (6) experienced severe personality disorder, mental retardation, and anorexia/bulimia nervosa.

Additionally, all included patients with AFD should be drug-naive or medication free for more than 1 week.

The inclusion criteria for patients with BD are as follows: (1) 16–60 years old, (2) meeting the DSM-5 criteria for major depressive episode of bipolar I disorder or bipolar II disorder, (3) scored 20 or higher on the HAMD-24, and (4) enough audiovisual ability and comprehensive ability to accomplish the interview.

The exclusion criteria for patients with BD are as follows: (1) severe medical or neurological problems; (2) female patients who are pregnant, planning to be pregnant, or breastfeeding; (3) high risk of suicide; (4) had electroconvulsive therapy, modified electroconvulsive therapy, or repetitive transcranial magnetic stimulation in the past 6 months; and (5) experienced severe personality disorder, mental retardation, and anorexia/bulimia nervosa.

The inclusion and exclusion criteria for HC are as follows: (1) 16–60 years old, (2) enough audiovisual ability and comprehensive ability to accomplish the interview, and (3) no history of mental disorder or serious somatic disease.

### Who will take informed consent? {26a}

The principal investigators (PIs), or trained investigators, who are fellows or residents in the clinical sites and delegated by the PIs, introduce the information about the iDoT-AFD study to potential participants. If any participant is willing to participate in the clinical trial, the informed consent will be signed before the eligibility screening.

### Additional consent provisions for collection and use of participant data and biological specimens {26b}

Blood sample collection and MRI scan have been clarified in the informed consent so no additional consents are provided.

### Interventions

#### Explanation for the choice of comparators {6b}

Treatment as usual (TAU) is used as a comparator. TAU allows any pharmacotherapy concordant with major practice guidelines for MDD.

#### Intervention description {11a}

All eligible patients with AFD are randomly allocated to one of the four treatment groups including “single application of selective serotonin reuptake inhibitor (SSRI) or serotonin-noradrenaline reuptake inhibitor (SNRI),” “SSRI/SNRI combined with mood stabilizer,” “SSRI/SNRI combined with quetiapine (≥ 150 mg/day),” or “TAU.” Mood stabilizer only means classical drugs including lithium and anticonvulsants. Quetiapine is chosen from atypical antipsychotics as suggested by guidelines [18].

#### Criteria for discontinuing or modifying allocated interventions {11b}

When recruited, participants are informed that they can reject to participate or leave the study at any time including but not limited to the following reasons.The participants withdraw consent to continue the study.The participants fail to accomplish the interview or have an unplanned pregnancy.It is inappropriate to continue the therapeutic schedule because of poor efficacy or intolerant side effects.Participants develop any serious adverse events possibly correlated with the interventions or anything else of the study.Participants develop serious suicidal ideation or risk of suicidal behavior.

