### Outcomes {12}

The following is the primary outcome:Clinical remission (examiner-rating), defined as total scores less than or equal to 7 on the HAMD-24 at the end of the 12th week

The following are the secondary outcomes:Clinical remission (self-rating), defined as total scores less than or equal to 5 on the QIDS-SR16 at the end of the 12th weekEarly improvement, defined as a ≥ 20% decrease from the baseline HAMD-24 at the end of the 2nd weekTreatment response, defined as a ≥ 50% decrease from the baseline HAMD-24 at the end of the 12th weekSeverity and incidence of adverse eventsThe time of treatment discontinuation for any causeWorking or learning time lost to any cause associated with the present study

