### Data collection and management

#### Plans for assessment and collection of outcomes {18a}

M.I.N.I International Neuropsychiatric Interview (MINI) [19] is used to conduct a comprehensive screening. HAMD-24 and Quick Inventory of Depressive Symptomatology (self-report) with 16 items (QIDS-SR16) [20] are applied to evaluate depressive symptoms, Hamilton’s Anxiety Scale (HAMA) [21] is used to assess anxious symptoms, HCL-32 is performed to recognize mania or hypomania symptoms, and Quality of Life Scale with 6 items (QOL-6) [22] is used to evaluate the life quality briefly. Additionally, family history, physical or mental comorbidity, the medication used before, prescription for this time, number of episodes, first-onset time and age, and duration of illness are also questioned and recorded. Adverse events are recorded in adverse events report (AER) forms when needed during the follow-up period. Cognitive function is assessed using the MATRICS Consensus Cognitive Battery (MCCB) [23]. MCCB consists of 10 subtests that mainly reflect the cognitive function of 7 cognitive domains including speed of processing, attention and vigilance, working memory, verbal learning, visual learning, reasoning and problem-solving, and social cognition.

After the 12-week randomized intervention, patients with AFD will be followed up until switching to BD for a maximum of 4 years. Face-to-face interviews, including clinical and neurocognitive assessments, MRI scans, and blood specimen collection, will be scheduled for 12 weeks, 1 year, and 4 years. The interim interviews of clinical assessments will be performed at 2 weeks, 4 weeks, 8 weeks, 6 months, 2 years, and 3 years through offline or online approaches. Patients with AFD will undergo a semi-structured interview at the follow-up time points to determine whether they have experienced mania or hypomania or have been diagnosed with bipolar disorder by psychiatrists during the interval since the previous follow-up. If a patient has experienced mania or hypomania or has been diagnosed with bipolar disorder by psychiatrists during the interval, multidimensional data will be recollected and follow-up will be terminated.

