## Statistical methods

### Statistical methods for primary and secondary outcomes {20a}

To evaluate the effectiveness of the 12-week treatment for patients with AFD, we plan to perform an intention-to-treat analysis to pursue our primary outcome. A mixed-effect model for repeated measures will be applied to analyze the main effects of interventions, time, and the interaction on HAMD total scores to find the optimal treatment for patients with AFD. Covariates like gender, age, education, and the baseline severity of depressive symptoms will be added to the model to correct the potential confounding effects.

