### Methods in analysis to handle protocol non-adherence and any statistical methods to handle missing data {20c}

The missing data will be managed using multiple imputation techniques. Sensitivity analysis will be further conducted using data from complete cases and data with replacing values.

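### The protocol merges stopping the allocated treatment with leaving the study, so week-12 remission can be missing for outcome-related reasons, and the one defined sensitivity analysis does not test this.

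*Protocol article*

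**What the plan says.** The heading of section {11b} concerns discontinuing or modifying the intervention, but its sentence is about the study: participants are told that "they can reject to participate or leave the study at any time including but not limited to the following reasons". The list includes "It is inappropriate to continue the therapeutic schedule because of poor efficacy or intolerant side effects", and also serious adverse events and serious suicidality. Withdrawn consent, failure to complete the interview and unplanned pregnancy are listed too.

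The primary outcome in {12} is remission, "defined as total scores less than or equal to 7 on the HAMD-24 at the end of the 12th week". Section {20a} states that "we plan to perform an intention-to-treat analysis to pursue our primary outcome", with a repeated-measures mixed model on HAMD totals. Section {20c} states that "The missing data will be managed using multiple imputation techniques". Its sensitivity analyses are complete cases and a second analysis with replaced values, which is not defined.

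On visits, {18a} states: "The interim interviews of clinical assessments will be performed at 2 weeks, 4 weeks, 8 weeks, 6 months, 2 years, and 3 years", offline or online, with face-to-face visits at week 12, 1 year and 4 years. On a switch to mania, hypomania or a bipolar diagnosis, "multidimensional data will be recollected and follow-up will be terminated". That rule is introduced by "After the 12-week randomized intervention, patients with AFD will be followed up until switching to BD for a maximum of 4 years".

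Section {14} allows for drop-out of up to 30%.

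**The concern.** A week-12 binary outcome analysed by intention to treat needs a week-12 score from as many randomised patients as possible, including those who have stopped the allocated drug. If stopping for failure or intolerance is handled as study exit, the missing scores are concentrated in patients who were unlikely to remit. An analysis plan that is not shown may specify the imputation model, but it cannot recover ratings that were never taken.

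Multiple imputation in its usual form assumes that, given the observed data, those who left resemble those who stayed. Complete-case analysis drops the same patients, so agreement between the two would give no reassurance about that assumption.

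Exit may also differ by arm. TAU allows any guideline-concordant pharmacotherapy ({6b}), so a failing TAU patient can change drugs and still be on the allocated strategy. The other three arms are defined by drug class ({11a}), and failure there may more readily end the allocated schedule. The trial is open-label, so knowing the allocation may also influence who leaves. What is at stake is which strategy appears best.

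**Working it through.** **The plan's own figure.** Inputs from {14}: d = 0.5, two-sided alpha 0.05, power 80%.

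- n per group = 2 × (1.960 + 0.842)² / 0.5² = 62.8, so 63. The exact t-test gives 64.
- With 30% drop-out: 63 / 0.70 = 90. Both stated figures reproduce.
- With the planned 120 per arm, 30% drop-out leaves 120 × 0.70 = 84 with a week-12 score and 36 without.

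**Gap within one arm.** Let d be the drop-out proportion, s the share of leavers who left through failure or intolerance, and p the remission rate in completers. Only the 30% ceiling for d is in the article; p and s are assumptions.

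- Imputing every leaver at the completer rate gives p.
- Counting failure leavers as non-remitters, and the rest at the completer rate, gives p(1 − d) + d(1 − s)p.
- Gap = d × s × p.

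| d | s | p = 30% | p = 40% | p = 50% |
|---|---|---|---|---|
| 0.30 | 1 | 9.0 | 12.0 | 15.0 |
| 0.30 | 0.5 | 4.5 | 6.0 | 7.5 |
| 0.20 | 1 | 6.0 | 8.0 | 10.0 |
| 0.10 | 1 | 3.0 | 4.0 | 5.0 |

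(gap in percentage points)

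**Gap between arms.** Assume completer remission of 50% (active) and 35% (TAU), with all leavers failing. Completer-rate imputation always reports 50 − 35 = 15 points. With failures counted as non-remitters:

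- 30% drop-out in both arms: 0.50 × 0.70 − 0.35 × 0.70 = 10.5 points.
- Active 30%, TAU 10%: 0.50 × 0.70 − 0.35 × 0.90 = 3.5 points.
- Active 10%, TAU 30%: 0.50 × 0.90 − 0.35 × 0.70 = 20.5 points.

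The imputed difference can therefore be too large or too small relative to that count.

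**Does the imputation model matter?** A simulation of 40,000 patients used assumed HAMD trajectories. Drop-out after week 4 or 8 depended on poor observed improvement, and 33.5% dropped out. HAMD was taken as rated at weeks 2, 4 and 8; the timeline figure is not shown.

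| Quantity | Remission |
|---|---|
| True, under continued treatment | 32.9% |
| Completers only | 43.4% |
| Imputation from baseline only | 42.5% |
| Imputation using weeks 2, 4 and 8 | 32.5% |
| All leavers counted as non-remitters | 28.8% |

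The baseline-only model overstates by 42.5 − 32.9 = 9.6 points. The model with interim scores is within 0.4 points of the truth under continued treatment, and 32.5 − 28.8 = 3.7 points above non-remitter coding. In this simulation drop-out followed observed scores by construction, so it cannot show what happens when leaving depends on outcomes not observed.

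**The case against.** The strongest reply is that the harm is inferred. Leaving is permitted, not required, and nothing states that week-12 ratings cease when treatment stops; the visit schedule makes no exception for patients off treatment. The imputation model is unstated and may sit in an analysis plan. Interim assessments exist, the planned mixed model uses repeated HAMD scores, and a suitable imputation removed the inflation in the simulation. The 30% is a ceiling for all causes, some unrelated to outcome. The undefined second sensitivity analysis might turn out to be a non-remitter analysis. All of this stands, and it limits the point to a risk whose size is conditional.

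It does not remove the gap in {11b}. Failure and intolerance are given there as reasons to leave the study, and continued rating after stopping treatment is provided for nowhere.

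Three stronger readings are tempting and are not supported:

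- *That remission will be inflated, by about 15 points.* That is the top of the range. It requires 30% drop-out, every leaver a failure, 50% remission in completers and imputation at the plain completer rate.
- *That the plan contradicts intention to treat.* Analysing all randomised patients as allocated, with missing outcomes imputed, is an ordinary form of it. Unclear retention weakens it but does not contradict it.
- *That the remission definition is wrong because it does not exclude switched patients.* The switch rule is framed mainly for the period after week 12, although its interviews arguably include weeks 2, 4 and 8. Data are recollected at the switch, and no early switch rate is given. A composite of remission and no switch is a debatable preference.

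**Conclusion.** The point holds as a gap in outcome collection with a conditional risk of bias. Followed as written, the protocol lets the week-12 HAMD-24 be missing for reasons tied to the outcome, and the only defined sensitivity analysis leaves out the same patients.

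Relative to counting failures as non-remitters, the overstatement within an arm is 9–15 points at 30% drop-out if all leavers failed, 4.5–7.5 points if half did, and 3–10 points at 10–20% drop-out if all did. Each range assumes 30–50% remission in completers and imputation at their rate. Relative to remission under continued treatment, it is near zero if interim scores are used and drop-out follows them. Against a target that counts remission on other care after leaving, the direction is unknown. The bias in the arm comparison can have either sign.

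**What to change.** 1. In {11b}, separate stopping the allocated treatment from withdrawing from the study. Collect HAMD-24 and QIDS-SR16 at the scheduled visits to week 12, online where needed, from everyone who has not withdrawn consent, including any patient who switches before week 12. This changes no treatment decision.
2. In {20c}, state that the imputation model includes the week 2, 4 and 8 HAMD scores.
3. Keep complete cases as descriptive only. Add an analysis counting missing as non-remission and a delta-adjusted (tipping-point) imputation by arm. Define the replaced-values analysis or drop it.
4. Report switches before week 12 by arm, with a sensitivity analysis counting them as non-remission. Leave the primary definition unchanged.

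The cost is wording, some extra ratings through online contacts that {18a} already uses for interim visits, and possibly lower remission rates in the sensitivity analyses. Recruitment was planned to finish before October 2022. For patients already past week 12, only items 2 to 4 can be applied, and they should be fixed before the outcome data are analysed.
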